### Outcomes and measures

The primary outcome of the trial is weight gain at 21 days since enrollment in the program, as measured by the z-score [38]. The z-score refers to the exact number of standard deviations greater or smaller than the median, and is used to monitor the growth of the infant relative to the expected intrauterine growth rate. It is standardized to population growth standards and superior to percentiles for infants whose size is outside of the normal range of a growth chart. As part of standard NICU practice infants are weighed at the same time each day with their diaper removed. Many infants are weighed on special scales built into their incubator. To decrease any risk of measurement bias nurses/parents are asked to first recalibrate the scales, then weigh the infant three times, and take the average weight. The bedside nurse charts the infant’s weight as per usual practice.

The secondary outcomes are: i) weight gain velocity at 21 days since enrollment and weight gain velocity from birth to 36 weeks corrected gestational age; ii) parent stress and anxiety; iii) breastfeeding rate at hospital discharge; iv) clinical outcomes including NICU mortality and major neonatal morbidities; v) safety as indicated by the number of critical incident reports per 1000 patient days; and vi) resource use including duration of oxygen therapy, duration of hospital stay, and potential cost savings due to reduced length of stay estimated using per diem costs [39].

The major neonatal morbidities include ≥ stage 2 necrotizing enterocolitis (NEC) defined according to Bell’s criteria [40]; bronchopulmonary dysplasia (BPD) defined as oxygen dependency at 36 weeks postmenstrual age or at the time of transfer to a level 2 centre [41]; nosocomial infection (NI) defined using the Center for Disease Control criteria [42]; ≥ stage 3 retinopathy of prematurity (ROP) classified according to the International Classification [43]; and ≥ grade 3 intraventricular hemorrhage (IVH) defined according to the criteria of Papile et al. [44] from cranial ultrasound during the first 28 days of life.

In both the intervention and control sites, parental stress and anxiety are measured using questionnaires (PSS:NICU and the State Trait Anxiety Index [STAI]) administered to parents at enrollment (Day 0) and Day 21 following enrollment. The PSS:NICU is a validated instrument to measure parents’ perceptions of stress within the NICU [32]. It comprises a 46-item self-report instrument that consists of four subscales that measure stress related to the: a) sights and sounds of the unit, b) appearance and behaviour of the infant, c) impact of the parents’ role and their relationship with their infant, and d) parents’ relationship and communication with the staff. The STAI is the definitive instrument for measuring anxiety in adults [45]. It is well validated, simple to use, and available in 40 languages. The STAI Form Y comprises of 40 items that can be completed in about 10 min, and measures state and trait anxiety. It provides a measure of the severity of the overall anxiety level.

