### Study participants

Eligible study infants include those who are: i) born at ≤ 33 weeks’ gestation; and ii) on no respiratory support or on low-level respiratory support (i.e., oxygen by cannula or mask, or non-invasive ventilation such as continuous positive airway pressure [CPAP], biphasic CPAP and nasal intermittent positive pressure ventilation). As most infants born at ≤ 33 weeks’ gestation are not discharged home until at least 36 weeks’ postmenstrual age, a minimum “dose” of 3 weeks of in-hospital intervention is ensured. An additional inclusion criterion at the intervention sites is that the primary caregiver parent must commit to spending a minimum of 6 h per day with her/his infant between the hours of 7 am and 8 pm to enable attendance at medical rounds and education sessions.

Infants excluded from the study are those who: i) are receiving palliative care; ii) have a major life-threatening congenital anomaly; iii) have a critical illness and are unlikely to survive; iv) are on a high level of respiratory support (mechanical ventilation, high-frequency oscillatory or jet ventilation, extra-corporeal membrane oxygenation); v) are scheduled for early transfer to another hospital; or vi) have parents with an inability to participate (e.g., health, family, social, or language issues that might inhibit their ability to integrate with the health-care team).

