### Enrollment

Parental consent is being obtained from families of eligible infants at both the intervention and control sites. For NICUs randomized to the FICare intervention arm, the site program coordinator approaches parents of all potentially eligible infants soon after admission to the NICU to explain the study verbally and deliver an information leaflet detailing the purpose and process of the study, as well as any possible detrimental effects of participation. Parents are screened to determine if there are barriers to their participation in the trial, and informed of the FICare education sessions, which they may attend regardless of whether they participate in the trial. Parents are then approached for informed consent when their baby becomes eligible (i.e., stable on CPAP). Families are enrolled in the trial, after consent is obtained (Day 0). All families approached are recorded in a patient eligibility log regardless of actual participation. Infants whose parents decline to participate in the study receive standard care at that site.

For NICUs randomized to the control arm, the site program coordinator approaches the parents of all potentially eligible infants for consent to collect infant data and information on parental stress and anxiety. The families of eligible infants at control sites are not screened to determine whether they would be willing to spend at least 6 h per day in the NICU as per the FICare protocol. The infants of parents who consent are enrolled in the study once they meet the inclusion criteria, and continue to receive standard care.

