### Data collection

Data collection at both the intervention and control sites commences at enrollment and continues for the trial duration (21 days) and through to discharge from the NICU. Data collection utilizes the existing CNN database platform [36] in Canada, and in Australia and New Zealand, the Australian and New Zealand Neonatal Network (ANZNN) data system [37]. Data collected include demographics, antenatal and obstetric risks, delivery complications, admission illness severity scores, and selected practices and outcomes related to this trial. At each site, a trained research assistant abstracts data daily from patient charts directly into a laptop computer using a customized data entry program with built-in error checking and a standard manual of definitions. SSL-encrypted data are electronically transmitted directly from the Canadian sites to the CNN Coordinating Centre for verification and further cleaning. The Australia and New Zealand sites collate data via the ANZNN data verification system and submit encrypted data in batches to the CNN Coordinating Center.

Questionnaires and surveys are administered to parents by site program coordinators, and are available online and on paper. Data entered into online surveys are automatically included in a survey database and answers from paper documents are entered into the database by the program coordinator. In addition, in the Australia and New Zealand sites parents have the preferred option of entering answers directly via smartphone to a purpose-built web-based dataset that is being collated at the ANZNN Coordinating Centre.

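### Two secondary outcomes, growth velocity from birth and IVH in the first 28 days of life, are counted over windows that open before enrolment, so pre-enrolment differences due to selection enter the FICare contrast.

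*Protocol article*

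**What the plan says.** Under Outcomes and measures, the first secondary outcome is a pair of growth velocities. One is taken over the 21 days after enrolment. The other is "weight gain velocity from birth to 36 weeks corrected gestational age". In the same section, IVH of grade 3 or more is one of the major neonatal morbidities and is ascertained "from cranial ultrasound during the first 28 days of life".

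Day 0 is later than birth. Under Enrollment: "Parents are then approached for informed consent when their baby becomes eligible (i.e., stable on CPAP"), and then "Families are enrolled in the trial, after consent is obtained (Day 0"). Under Study participants, infants "born at ≤ 33 weeks’ gestation" may enter, but those who "are on a high level of respiratory support (mechanical ventilation, high-frequency oscillatory or jet ventilation, extra-corporeal membrane oxygenation") may not. An infant who is ventilated after birth can therefore enrol only after coming off the ventilator.

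Limitations and feasibility states that families are recruited after sites have been randomised, that the recruiting coordinators know their site's allocation, and that the 6 h commitment is a condition of entry at FICare sites only.

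**The concern.** Randomisation was of units, but the infants analysed are those who were later enrolled, under entry rules that differ by arm. Anything that happened before Day 0 is a property of the infants who got in. It belongs on the baseline side of the comparison.

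With a clock that starts at birth, two things follow:

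- **Selection can appear as effect.** If enrolled FICare infants had more or less severe IVH, or better or worse early growth, before Day 0 than enrolled control infants, that difference is tabulated in the outcome comparison as benefit or harm. The documents do not allow its direction to be predicted.
- **The velocity contrast shrinks.** A gain achieved after Day 0 is averaged over a period that includes the weeks before it.

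At stake is the interpretation of one growth measure and one component of the morbidity list, both secondary.

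**Working it through.** **The plan's own figure.** The article gives no figure for these two outcomes. Its one design figure, 675 per arm, is for the primary outcome, and it reproduces closely:

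- Common SD: √((0.57² + 0.43²)/2) = 0.505.
- Per arm before clustering, for a difference of 0.11, two-sided 5% and 80% power: 2 × (1.960 + 0.842)² × 0.505²/0.11² ≈ 331.
- Design effect with minimum-variance weights: Σm/Σ[m/(1 + 0.01(m − 1))]. I assume 3 large and 5 small sites per arm, with sizes in proportion to 315 and 113. Solved together with the sample size, this gives 625 evaluable, and 625/0.9 ≈ 695 enrolled, within 3% of 675.
- At 675 × 0.9 = 607.5 evaluable, the design effect is 1.865 and power is 79.4%.

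The sample size is not in question.

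**Inputs for this point.** The 36-week end point and the 28-day IVH window come from Outcomes and measures. Day 0 comes from Enrollment. Age at enrolment, *a* in weeks, is not given, so every value of it below is an assumption.

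**Growth velocity.** Suppose FICare adds *d* grams between Day 0 and 36 weeks, and velocity is gain divided by time. For gestational age GA at birth:

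- difference in velocity from Day 0: d/(36 − GA − a)
- difference in velocity from birth: d/(36 − GA)
- ratio of the second to the first: (36 − GA − a)/(36 − GA)
- share of the window before Day 0: a/(36 − GA)

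| Birth (weeks) | a = 1 | a = 2 | a = 3 |
|---|---|---|---|
| 26 | 1/10 = 10% | 2/10 = 20% | 3/10 = 30% |
| 30 | 1/6 = 17% | 2/6 = 33% | 3/6 = 50% |
| 32 | 1/4 = 25% | 2/4 = 50% | 3/4 = 75% |

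The entries are shares before Day 0. For birth at 30 weeks, the velocity difference from birth is 83%, 67% or 50% of that from Day 0. The difference *d* itself is the same in both.

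**IVH.** Days of the 28-day window left after Day 0 are 28 − 7a: 21, 14 and 7 for a = 1, 2 and 3, and none for a = 4. An infant enrolled after day 28 can contribute only IVH that was already there.

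**Selection, for illustration only.** Take no treatment effect, 607.5 evaluable per arm, the primary outcome's design effect of 1.865, and no covariate adjustment. The standard error in SD units is √(2 × 1.865/607.5) = 0.078. A pre-existing difference between arms in the whole-window outcome would then raise the two-sided 5% false-positive rate as follows:

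| Assumed imbalance (SD) | False-positive rate |
|---|---|
| 0.05 | 10% |
| 0.10 | 25% |
| 0.20 | 72% |

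The documents supply no estimate of the imbalance. The table shows only that a modest one would matter.

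**Does the planned adjustment remove it?** Statistical analysis and Limitations and feasibility list covariates that include gestational age, illness severity at admission and age at enrolment, and propensity scores are considered. Neither list includes IVH or weight gain up to Day 0. Adjustment can reduce imbalance in measured factors, but pre-enrolment events stay in the outcome.

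**The case against.** The other side has a good deal to say, and much of it stands.

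- **Growth from enrolment is already covered.** The primary outcome and the 21-day velocity both start at Day 0, and a longitudinal model of weight is planned. This stands: no main growth conclusion rests on the birth-anchored measure alone.
- **Birth is a fixed origin, whereas Day 0 depends on when an unblinded coordinator obtains consent.** This is a fair reason to keep the birth-anchored velocity as a description, but not to treat it as a treatment contrast.
- **Selection is disclosed.** The article plans to compare enrolment rates, adjust, and report residual bias. This softens the concern but does not remove it, for the reason given in the working.
- **Pre-enrolment time is not wholly unexposed.** Staff are trained across the unit, and parents may attend education sessions whether or not they join the trial. Some FICare exposure may precede Day 0, so the shrinkage may be less than the formula gives.

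A reader might also infer three stronger points that the documents do not support:

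- **A contradiction with Data collection**, which says "Data collection at both the intervention and control sites commences at enrollment". That describes when abstraction starts. The same section lists antenatal and delivery data, which necessarily predate enrolment.
- **A fault in necrotising enterocolitis, nosocomial infection, oxygen days or length of stay** because no start point is printed. The article states no wrong one, and it refers to a manual of definitions. A condensed article may leave this to the full protocol.
- **A definite loss of power.** Averaging over a longer interval rescales noise as well as effect, and the documents do not give the variance of pre-enrolment growth.

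**Conclusion.** The point holds for two stated definitions: the velocity from birth to 36 weeks, and IVH of grade 3 or more in the first 28 days of life. Both include time before Day 0. Because recruitment is unblinded, follows site randomisation and uses different entry criteria by arm, pre-enrolment differences can enter the comparison and be read as an effect of FICare.

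The size cannot be fixed from the documents. Under the assumption of enrolment at 1 to 3 weeks of age for birth at 30 weeks, 17% to 50% of the growth window and 7 to 21 of the 28 IVH days precede Day 0. The first scales down a velocity difference but leaves the difference in grams unchanged.

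A reader might take this as a threat to the trial's main result. It is not: the primary outcome, the 21-day velocity and the sample size are unaffected. It is a worthwhile and cheap correction to secondary definitions.

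**What to change.** - Define the longer growth velocity from Day 0 to 36 weeks. The velocity from birth may be kept as descriptive.
- Count as an outcome only IVH of grade 3 or more first seen after Day 0.
- Report IVH of that grade already present at Day 0 in the baseline table, by arm, and use it to assess selection.
- If the full protocol does not already do so, apply the same origin to the other morbidities. For infection, count any new episode after Day 0, so that an infant with an earlier episode is not dropped.

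The change is one of wording and needs charted weights and the dates of scans and diagnoses. The cost is fewer counted IVH events, and so less precision for that outcome. Where no scan was done before Day 0, a bleed first seen afterwards may still have begun earlier, and the report should say so.

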### Sample size calculation

The proposed sample size of 675 infants in each arm of the trial was estimated for the primary outcome of weight gain at 21 days post-enrollment, as measured by the change in z-score (z-score at Day 21 – z-score at enrollment), using preliminary data from the FICare pilot study available at the time of trial design. These data included 20 infants in the FICare group with mean change in z-scores of 0.58 (standard deviation of 0.57), and 40 matched controls with mean change in z-scores of 0.42 (standard deviation of 0.43). Based on this result (38 % increase in mean z-score change) and Levin’s study [9], we anticipated at least a 25 % increase in mean z-score change in the FICare group. The sample size was estimated assuming the above standard deviation estimates from the preliminary data, and using Kerry’s method [46, 47] for unequal cluster sizes, given that 16 sites (6 large with average size of 315 eligible infants per year, and 10 small with average size of 113 eligible infants per year) had agreed to participate in the trial at that time. The sample size of 675 infants per arm has 80 % power to detect a ≥ 25 % difference (absolute difference of 0.11) in z-score change assuming a significance level of 0.05, intra-cluster correlation coefficient (ICC) of 0.01 [48, 49], and a 10 % drop-out rate.

The estimated sample size is feasible to achieve given that approximately 3200 eligible infants are admitted each year to the 16 sites committed at the time of trial design. We also note that statistical power and the number of eligible infants has been increased by recruitment of additional sites; in total 19 Canadian sites (10 large sites and 9 small sites) and 7 Australian/New Zealand sites (all small) have been randomized and approximately 4300 infants are eligible for enrollment annually.

### Statistical analysis

The unit of analysis will be the individual infant, and all analyses will be based on the intention to treat principle. The distribution of baseline characteristics in the study population will be summarized at the individual and cluster level within each FICare and control groups, using descriptive statistical methods. The primary outcome of weight gain at 21 days post enrollment, will be compared between the FICare and control groups using Student’s *t*-test adjusted for the inflation factor (or design effect) with a minimum variation weight correction [46, 47] to account for intra-cluster correlation and imbalance of cluster sizes. In addition, a two-level hierarchical linear regression model will examine the primary outcome, accounting for clustering, and potential confounders including patient-level characteristics (birth weight, gestational age, small for gestational age, gender, multiple births, admission illness severity, caesarean section, chorioamnionitis, maternal hypertension or diabetes, maternal education, parity) and NICU-level covariates (NICU size, teaching institution).

Secondary outcomes will be compared between the FICare and control groups using similar methods including the Student’s *t*-test for continuous variables and the Chi-square test for categorical variables adjusted for clustering [50, 51], as well as hierarchical linear or logistic regression models, as appropriate. Furthermore, weight change over time will be examined longitudinally using multivariable multi-level hierarchical models to compare the rate of change in weight gain between infants from the two trial arms.

While we realize that multiple comparisons are a concern when more than one analysis of the data is performed, we are not interested in the joint confidence region for all of our hypotheses at once. Rather, we are interested in them one at a time. Under these conditions, Rothman and Greenland [52, 53] argue that “multiple inference procedures … are irrelevant, inappropriate and wasteful of information” because they produce improperly imprecise single intervals.

Prior to data unmasking and analyses, issues relating to missing data and potential sources of bias will be examined and appropriate correction methods determined.

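### The infant is the stated unit for every analysis, so parents of multiples are over-weighted in the stress and anxiety outcomes, and sibling correlation is not modelled for the primary outcome

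*Protocol article*

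**What the plan says.** All references are to the protocol article.

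- **Unit.** Statistical analysis opens with "The unit of analysis will be the individual infant, and all analyses will be based on the intention to treat principle". No outcome is exempted.
- **Primary model.** "a two-level hierarchical linear regression model will examine the primary outcome, accounting for clustering". Multiple birth appears only in the list of patient-level covariates: "small for gestational age, gender, multiple births, admission illness severity".
- **Secondary outcomes.** "Secondary outcomes will be compared between the FICare and control groups using similar methods", with hierarchical linear or logistic models where suitable.
- **Parental outcomes.** Outcomes and measures lists "ii) parent stress and anxiety" as a secondary outcome. The instruments, PSS:NICU and STAI, are "administered to parents at enrollment (Day 0) and Day 21 following enrollment".
- **Multiples are eligible.** The exclusion list under Study participants does not mention them, the covariate list presupposes them, and the Intervention section allows for a parent caring for more than one infant.
- **Sample size.** The calculation uses one correlation, a NICU-level ICC of 0.01. No sibling correlation is given.

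No section names a family level, a one-record-per-family rule, or the parent as the unit for the questionnaires.

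**The concern.** The stated unit and the source of the data do not match for the parental outcomes. A questionnaire score belongs to a parent. If the analysis file has one row per infant, a mother of twins supplies two rows, probably identical. The comparison then averages over infants rather than parents, which is a different quantity, and it contains repeated observations.

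For infant outcomes the issue is milder. Siblings share parents, feeding and, at FICare sites, the amount of intervention received, so their weight gain is likely to be correlated beyond what they share with other infants in the unit. A multiple-birth covariate shifts the expected value for multiples; it does not describe correlation within a pair. With only infant and NICU levels, siblings are treated as independent given their NICU.

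At stake are the target and precision of a named secondary outcome, and a modest amount of power for the primary one.

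**Working it through.** **Inputs from the Sample size calculation section.** 675 infants per arm, 10% drop-out (607.5 evaluable), difference 0.11 (25% of 0.42 = 0.105), SDs 0.57 (n = 20) and 0.43 (n = 40), ICC 0.01, alpha 0.05 (taken as two-sided), and 16 sites averaging 315 (6 large) or 113 (10 small) eligible infants a year.

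**Assumptions, not in the documents.** Three large and five small sites per arm; twins only; share of infants with an enrolled co-twin p = 0.20-0.30; sibling correlation r = 0.5-0.7 for weight gain and r = 1 for a duplicated parent score.

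**1. The plan's own figure.** With minimum-variance weights, effective n per arm = sum over sites of m / (1 + (m - 1) x 0.01). Splitting 607.5 in proportion to 315 and 113 (total 3 x 315 + 5 x 113 = 1510) gives m = 126.7 and 45.5, so effective n = 3 x 56.14 + 5 x 31.47 = 325.8. With SD = sqrt((0.57² + 0.43²)/2) = 0.505, SE = 0.505 x sqrt(2/325.8) = 0.0396, and power = Phi(0.11/0.0396 - 1.96) = 79.4%. With difference 0.105 and the pooled SD of 0.480, power is 79.7%. The stated 80% is reproduced with no sibling term.

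**2. Families behind the records.** Families = 675 x (1 - p/2): 607.5 at p = 0.20 and 573.75 at p = 0.30, so about 574-608 per arm before drop-out. Families of twins would be 0.10/0.90 = 11% to 0.15/0.85 = 18% of families but carry 20-30% of the weight.

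**3. Duplicated parent scores, fixed ICC.** The sibling term adds to the NICU design effect: DE = 1 + (m - 1) x 0.01 + p x (r - 0.01). With 1350/26 = 52 infants per site, the NICU part is 1.51. For r = 1 the unmodelled factor is (1.51 + 0.198)/1.51 = 1.13 at p = 0.20 and (1.51 + 0.297)/1.51 = 1.20 at p = 0.30. Type I error = 2 x (1 - Phi(1.96/sqrt(factor))) = 6.5% and 7.3%.

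**4. Simulation check.** 26 sites, 52 infants each, 30% of infants in twin pairs, 6000 runs per setting, normal critical value:

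| Sibling correlation | ICC fixed at 0.01 | Between-NICU variance estimated |
|---|---|---|
| 0.01 (no excess) | 4.9% | 5.7% |
| 0.5 | 5.7% | 5.9% |
| 0.7 | 6.8% | 6.2% |
| 1.0 (duplicated) | 7.9% | 6.1% |

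The Monte Carlo standard error is about 0.3 points. Steps 3 and 4 together give about 6.5-8% for duplicated scores with a fixed ICC. With an estimated ICC the change is close to simulation noise, because siblings sit inside the randomised NICU and their correlation feeds into the observed between-NICU variance.

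**5. Power for weight gain.** Adding p x (r - 0.01) to each site's design effect in step 1 (difference 0.11, SD 0.505):

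| p | r | Effective n per arm | Power |
|---|---|---|---|
| 0 | - | 325.8 | 79.4% |
| 0.20 | 0.5 | 308.8 | 77.3% |
| 0.20 | 0.7 | 302.4 | 76.4% |
| 0.30 | 0.5 | 300.9 | 76.2% |
| 0.30 | 0.7 | 291.9 | 74.9% |

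The loss is 2.1 to 4.5 points. By the same method, the number needed per arm rises from 696 to 765-840.

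**The case against.** The strongest reply is that the opening sentence is the usual cluster-trial declaration that the individual, not the NICU, is analysed. Elsewhere the article thinks in families: Enrollment enrols families, and Limitations and feasibility plans drop-out and imputation work on families. On that view the questionnaires would naturally be analysed per parent, and the detail belongs in an analysis plan that is not shown.

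Part of this stands. The article never says that parents are counted more than once; that follows only from applying the infant unit to a parent questionnaire. Nor does it say whether parents of twins answer PSS:NICU once or per infant. Two of its subscales concern the infant, so identical scores are an assumption there. But the sentence is a stated rule covering all analyses, so an analysis plan that follows it inherits the mismatch and one that corrects it departs from the published rule.

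The objection on size also largely stands. Siblings are nested in the randomised unit, so an estimated ICC absorbs nearly all the effect on type I error. The article does not say that the planning ICC will be plugged into the adjusted *t*-test, and 0.01 was chosen for weight gain, not parent scores. The extra sites also help. With 13 equal sites per arm (a favourable simplification), m = 607.5/13 = 46.7, DE = 1.457, effective n = 417 and power = 88%. Adding the largest sibling term above, 0.3 x 0.69 = 0.207, gives effective n = 365 and power = 84%.

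**Conclusion.** The point holds, at moderate size. For PSS:NICU and STAI the stated unit is wrong: taken literally, it gives families of multiples extra weight and may duplicate records. Estimating the ICC does not cure the weighting. For the primary outcome, sibling correlation is neither modelled nor allowed for in the sample size. On the 16-site basis of the published calculation this costs roughly 2-5 points of power, given p = 0.20-0.30 and r = 0.5-0.7, both assumed.

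Three stronger readings are tempting, and the documents do not support them:

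- **That type I error is 7-9%.** Applying 1 + p x r to the whole variance (1.20-1.35 for p = 0.20-0.35, r = 1) gives 7.4-9.2%. That treats the sibling term as multiplying a test already inflated for NICU clustering, and it needs a fixed ICC. The supportable figure is about 6.5-8% under a fixed ICC, and almost no change otherwise.
- **That every model excludes a family level.** Two levels are specified for the primary-outcome model only. The secondary and longitudinal models neither name nor rule out a family level.
- **That the primary comparison is invalid, or biased in a known direction.** Neither is shown.

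**What to change.** Amend the opening of Statistical analysis to state the unit by type of outcome:

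- **Parental outcomes (PSS:NICU, STAI):** one record per responding parent, clustered by NICU, and by family where both parents respond.
- **Infant outcomes:** infants within family within NICU, through a family random effect. Alternatively, keep the two-level model and add a sensitivity analysis with one weighted record per family.

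The cost is a family identifier linking siblings and a slightly more complex model. No new outcome data are needed. The change can be settled in the review that the article already schedules before unmasking.
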